#### Resistance training program.

Participants assigned to the RT group will undergo a 12-week exercise program comprising 3 weekly sessions. Before the intervention begins, all participants will perform a one-repetition maximum (1RM) test to elucidate baseline muscle strength and determine individualized training intensities. The 1RM will be estimated using a submaximal testing approach, in which participants perform 3–5 repetitions at approximately 60%–80% of their perceived maximum load for selected TheraBand-based resistance exercises (e.g., knee extension, hip abduction, elbow flexion). The Brzycki formula (estimated 1RM (kg) = submaximal weight (kg)/ (1.0278 − 0.0278 × maximal number of repetitions)) [46] will be applied to estimate 1RM values from these submaximal repetitions. All tests will be supervised by experienced physiotherapists, and standardized rest intervals of 1 minute will be maintained between sets to minimize fatigue. Based on the estimated 1RM, participants will be assigned an appropriate TheraBand (color-coded by resistance level: yellow, red, green, blue, black) and instructed to maintain a specific elongation length (e.g., 100% or 200%) to approximate the desired resistance. This allows adjustment of load to approximately 70% of 1RM, consistent with elastic resistance training literature [47,48]. To enhance precision, perceived exertion will be concurrently monitored using the Borg CR-10 scale [49,50], ensuring training load consistency throughout the intervention. The training intensity will be set at 70% of the 1RM for the entire 12-week program. Each training session will comprise 3 phases: a 5-minute warm-up, the main 30-minute RT exercises, and a 5-minute cool-down. During the 5-minute warm-up, participants will mainly perform neck, shoulder, lower back, hip, knee, and ankle stretches. Participants will perform three sets of 10 repetitions for each exercise, with a 1-minute rest between sets. The exercises will be performed using a TheraBand to reduce the stress of free weights on participants’ joints and increase their motivation to engage in RT [51,52]. RT exercises will focus on lower limb muscles (knee flexion/extension, hip abduction), upper limb muscles (shoulder extension/abduction, elbow flexion/extension), and core muscles (including chest press). Following these exercises, participants will perform a 5-minute cool-down protocol matching the warm-up in structure.

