#### Combined RT and VT program.

The RVT group will receive a 12-week RT combined with a VT program thrice weekly. The intensity of RT in the RVT group will be adjusted based on each participant’s 1RM test results. The intensity will be set at 50% of 1RM for the first 4 weeks, increased to 55% during weeks 5–8, and further increased to 60% during weeks 9–12. This progressive design was adopted to improve tolerance and adherence, as participants in the RVT group receive an additional neuromuscular stimulus from vibration training. A gradual intensity progression has been shown to enhance safety and minimize musculoskeletal discomfort in older adults when initiating vibration-based exercise interventions. This approach is supported by previous studies [53,54], which recommended lower initial intensities in vibration training to allow neuromuscular adaptation In contrast, the RT group, which does not receive vibration stimulation, follows standard sarcopenia guidelines and begins directly at 70% 1RM. Each workout will follow the same structure as the RT group, including warm-up, RT, and cool-down. Each RT session will be followed by an additional VT session, with the same parameters as those of the VT group.

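### The 1RM formula needs the maximal number of repetitions but is applied to 3–5 submaximal ones, so the stated training intensities may overstate the dose delivered

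*Protocol article*

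**What the plan says.** All quotations are from the protocol article.

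- **Type of test** (Resistance training program): "The 1RM will be estimated using a submaximal testing approach". In it, "participants perform 3–5 repetitions at approximately 60%–80% of their perceived maximum load".
- **Formula** (same section): estimated 1RM is "submaximal weight (kg)/ (1.0278 − 0.0278 × maximal number of repetitions"), and it "will be applied to estimate 1RM values from these submaximal repetitions".
- **RT dose** (same section): a band colour and an elongation are chosen from the estimate. "This allows adjustment of load to approximately 70% of 1RM", and "The training intensity will be set at 70% of the 1RM for the entire 12-week program". Alongside this, "perceived exertion will be concurrently monitored using the Borg CR-10 scale".
- **RVT dose** (Combined RT and VT program): "The intensity of RT in the RVT group will be adjusted based on each participant’s 1RM test results". The levels are 50%, 55% and 60% of 1RM over three successive four-week blocks. This section also contrasts RVT with RT, which it describes as starting at 70% of 1RM in line with standard sarcopenia guidelines.

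**The concern.** A repetition-based 1RM formula works because the number of repetitions someone can just complete at a given load shows how far that load lies below the maximum. A count that stops short of the limit carries no such information. It makes the load look closer to the maximum than it is, and the estimated 1RM comes out too low.

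The printed formula asks for a maximal count, and the text then supplies a fixed, small count described as submaximal. The protocol's own training prescription points the same way: RT participants do three sets of 10 at 70% of 1RM, the middle of the test-load range, where the test asks for only 3–5.

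Both resistance arms are defined by this estimate. If it is too low, participants train lighter than the percentages say. The description of RT as guideline-level 70% training would not hold, and anyone replicating 70% of a properly measured 1RM would deliver a heavier dose than the trial did.

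**Working it through.** **Inputs.** From Resistance training program: test load w = 0.60–0.80 of perceived maximum, repetitions r = 3–5, the formula, and RT at 70%. From Combined RT and VT program: RVT at 50/55/60%. Assumed, because the article gives no figure: q = perceived maximum / true 1RM, taken as 1.0 first and then varied.

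**Step 1. When the stated percentages are right.** Setting estimated equal to true 1RM at q = 1 and inverting the formula gives r = (1.0278 − w)/0.0278.

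- w = 0.60: 0.4278/0.0278 = 15.4 repetitions
- w = 0.70: 0.3278/0.0278 = 11.8
- w = 0.80: 0.2278/0.0278 = 8.2

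With these counts the nominal 70% and 50/55/60% are recovered. Conversely, 3 to 5 repetitions are maximal only at loads of 94.4% to 88.9% of 1RM.

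**Step 2. What 3–5 repetitions give.** The denominator 1.0278 − 0.0278r is 0.9444 (r = 3), 0.9166 (r = 4) and 0.8888 (r = 5). At q = 1, estimated/true 1RM = w/denominator, and the true intensity is the nominal percentage times that ratio.

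| Test set | Estimated/true 1RM | RT 70% | RVT 50% | RVT 55% | RVT 60% |
|---|---|---|---|---|---|
| 3 at 60% | 0.60/0.9444 = 0.635 | 44.5% | 31.8% | 34.9% | 38.1% |
| 4 at 70% | 0.70/0.9166 = 0.764 | 53.5% | 38.2% | 42.0% | 45.8% |
| 5 at 80% | 0.80/0.8888 = 0.900 | 63.0% | 45.0% | 49.5% | 54.0% |

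**Step 3. Dependence on q.** The ratio becomes q × w/denominator.

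- q = 0.8: nominal 70% is 35.6–50.4%.
- q = 1.2: nominal 70% is 53.4% for 3 at 60% and 64.2% for 4 at 70%.
- No shortfall: q = 0.8888/0.80 = 1.11 (5 at 80%), 0.9166/0.70 = 1.31 (4 at 70%), 0.9444/0.60 = 1.57 (3 at 60%).

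**Step 4. Direction.** A completed count cannot exceed the maximal count for that load. A smaller r gives a larger denominator, so by the formula the estimate cannot exceed true 1RM. Arithmetic results above nominal are therefore not achievable. For example, 5 at 80% with q = 1.2 gives 0.80 × 1.2 = 96% of true 1RM, where the formula allows only (1.0278 − 0.96)/0.0278 = 2.4 repetitions.

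**The case against.** The strongest defence is that the formula is printed correctly: there, submaximal describes the weight and maximal describes the repetitions. The later phrase could be loose wording for repetitions to the limit at a submaximal weight, and nothing says outright that participants stop early. That reading cannot be excluded. But it goes against the plain sense of the sentence, and by the formula it works only if participants overrate their maximum by 11–57%. The article gives no reason to expect that. Even if it is what was meant, the wording needs correcting.

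Second, the size rests on an unknown ratio, and the extremes pair the fewest repetitions with the lightest load. This stands. With the more natural pairing at q = 1, 5 at 60% gives 0.60/0.8888 = 0.675 and 3 at 80% gives 0.80/0.9444 = 0.847, so nominal 70% is about 47–59%. The range is narrower but still well short of 70%.

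Third, the load is called approximate, is set by band and elongation, and is checked with Borg CR-10. Approximation would excuse scatter, but this error runs one way. Borg monitoring might correct part of it. The article states no target rating, which may simply be left to a fuller document and is not counted as a fault here, so a correction cannot be assumed.

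Fourth, moving to repetitions-to-limit testing now would change the intervention partway through recruitment. That is right, and it shapes the fix.

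**Conclusion.** The point holds as a conditional one. As written, the test gives the formula a count that it is not built for. If the sets are not taken to the limit, the estimated 1RM is too low and the stated intensities in both resistance arms overstate the dose. With perceived equal to true maximum, the estimate is 0.64–0.90 of true 1RM. Nominal 70% is then 44.5–63.0%, and RVT 50/55/60% are about 32–45%, 35–50% and 38–54%. The size depends on two things that the article does not settle: whether sets are maximal, and how perceived maximum relates to true maximum.

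A reader might infer more, but the article does not support it:

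- **That the trial's comparisons are biased.** All participants take the same test, so RT and RVT loads are scaled alike on average and their ratio is kept. The randomised comparison of regimens as delivered and the primary analysis are unaffected.
- **That the delivered dose is known to be too low.** It is probable on the wording, not established.
- **That the dose might equally be too high.** By the formula, a non-maximal count cannot produce that.

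What is affected is the stated dose, the statement that RT starts at guideline-level 70% of 1RM, and replicability. This should be corrected, but it does not threaten the trial's inference.

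**What to change.** Record for each 1RM test the load, the repetition count and whether the set was taken to the limit. Then:

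- **If the sets are maximal:** say so, and replace the wording that calls the repetitions submaximal.
- **If they are not:** leave the loading as it is, so that each arm stays consistent. Report the dose as band colour, elongation and Borg CR-10 rating. Describe 70% and 50/55/60% as nominal values from a non-maximal test that probably overstate true intensity, and qualify the guideline statement in Combined RT and VT program accordingly.

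The cost is one extra form field, a wording change and a less favourable stated intensity.

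Testing future participants to their limit is optional only. At mid-range it would raise the estimated 1RM, and so the delivered load, by 1/0.764 − 1 = about 31% for later participants in both resistance arms. Recruitment has run since 30 April 2024 (Trial registration and status), so each arm would then contain two doses. A change to the intervention would also have to be reported to the Ethics Committee (Ethics and dissemination), and the test would be more demanding for participants aged 65–80.

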#### Vibration training program.

The VT cohort will receive VT sessions 3 times/week for 12 weeks. VT will be performed using a vibrating platform (Pro5 AIRdaptive; Power Plate, USA) that produces vertical vibrations. Each session will last approximately 19 minutes, comprising a 5-minute warm-up, a 9-minute vibration period, and a 5-minute cool-down. The vibration frequency will gradually increase to 40 Hz with a peak-to-peak amplitude of 4 mm. Participants will stand barefoot on the vibrating platform during VT, maintaining a 60° knee flexion while grasping the vibrating rope with both hands for balance. The VT will be maintained for 1.5 minutes and repeated for four sets each day [33], with a 1-minute rest between each set.

#### Combined RT and VT program.

The RVT group will receive a 12-week RT combined with a VT program thrice weekly. The intensity of RT in the RVT group will be adjusted based on each participant’s 1RM test results. The intensity will be set at 50% of 1RM for the first 4 weeks, increased to 55% during weeks 5–8, and further increased to 60% during weeks 9–12. This progressive design was adopted to improve tolerance and adherence, as participants in the RVT group receive an additional neuromuscular stimulus from vibration training. A gradual intensity progression has been shown to enhance safety and minimize musculoskeletal discomfort in older adults when initiating vibration-based exercise interventions. This approach is supported by previous studies [53,54], which recommended lower initial intensities in vibration training to allow neuromuscular adaptation In contrast, the RT group, which does not receive vibration stimulation, follows standard sarcopenia guidelines and begins directly at 70% 1RM. Each workout will follow the same structure as the RT group, including warm-up, RT, and cool-down. Each RT session will be followed by an additional VT session, with the same parameters as those of the VT group.

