### Sample size determination

The required sample size was calculated using G*Power (version 3.1.9.7, Germany) for a two-way repeated-measures ANOVA (within-between interaction), with a significance level of α = 0.05, power (1–β) = 0.80, and four intervention groups (Control, RT, VT, RVT). The effect size was set to f = 0.40 (partial η^2^ = 0.14), which reflects a moderate-to-large effect based on prior studies assessing changes in IGF-1 expression and physical function following resistance and vibration training in older adults. The primary endpoint for power estimation was the change from baseline to 12 weeks, representing the completion of the supervised intervention. The 24-week point is considered a follow-up to assess sustainability but was not included in the power calculation. Considering a 20% dropout rate, the minimum required sample size was estimated at 73 participants [45]. Therefore, we plan to recruit 96 individuals (24 per group) to ensure adequate statistical power. In view of multiple primary outcomes and six pairwise comparisons among four groups, Holm–Bonferroni correction will be applied to adjust for potential inflation of type I error. Additionally, the hypothesis is based on additive rather than synergistic effects between RT and VT. Hence, interaction effects were not included in the sample size model but will be explored post hoc.

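### The combined arm trains at a lower resistance load than the RT arm in every week, so neither RVT vs RT nor the RT-by-VT interaction can show vibration's added effect or additivity

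*Protocol article*

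**What the plan says.** All of this is in the protocol article.

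- **RT arm** (Resistance training program): "The training intensity will be set at 70% of the 1RM for the entire 12-week program". Load is set through elastic-band colour and elongation, so it is approximate: "This allows adjustment of load to approximately 70% of 1RM".
- **RVT arm, resistance** (Combined RT and VT program): "The intensity will be set at 50% of 1RM for the first 4 weeks", then 55% in weeks 5–8 and 60% in weeks 9–12. The session structure is that of the RT arm, and no extra volume is described to offset the lower load.
- **RVT arm, vibration** (same section): "Each RT session will be followed by an additional VT session, with the same parameters as those of the VT group".
- **Reason given** (same section): "This progressive design was adopted to improve tolerance and adherence". Safety is also cited.
- **Hypothesis and comparisons** (Sample size determination): "the hypothesis is based on additive rather than synergistic effects between RT and VT", and "interaction effects were not included in the sample size model but will be explored post hoc". The Holm–Bonferroni correction covers "six pairwise comparisons among four groups", so RVT vs RT is one of the planned comparisons on the primary outcomes.
- **Interpretation**: the Discussion gives as an aim the amplification of pathway effects when the two modalities are used together. Neither the Statistical analysis section nor the limitations in the Discussion mention the unequal resistance dose.

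**The concern.** The four arms look like a 2×2 layout (resistance yes/no, vibration yes/no), and the stated hypothesis treats them that way. But the resistance programme differs according to whether vibration is present: a constant 70% without it, a 50/55/60% ramp with it. RVT vs RT therefore changes two things at once, and the interaction contrast mixes two different resistance programmes.

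What is at stake is the conclusion about how the modalities combine. If response rises with load, two effects that add exactly would give a negative interaction and a smaller RVT vs RT difference, which could be read as vibration adding little. Conversely, a null interaction, naturally read as support for additivity, could hide a real synergy.

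**Working it through.** **1. Prescribed loads** (from the two intervention sections)

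| Weeks | RT | RVT | RVT/RT |
|---|---|---|---|
| 1–4 | 70% | 50% | 0.714 |
| 5–8 | 70% | 55% | 0.786 |
| 9–12 | 70% | 60% | 0.857 |
| Mean | 70% | 55% | 0.786 |

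RVT is lower in all 12 weeks, by 20, 15 and 10 percentage points.

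**2. What each contrast estimates.** Let r be the effect of RT at 70%, v the effect of vibration, I the true interaction, and g the share of r kept at the RVT load. Arm means relative to control are: control 0, RT r, VT v, RVT g·r + v + I. Then:

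- RVT − RT = v + I − (1 − g)r
- RVT − RT − VT + control = I − (1 − g)r
- RVT − VT = g·r + I

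The first two carry the term (1 − g)r, which is zero only if g = 1. With equal loads they would reduce to v + I and to I. The third contrast has identical vibration on both sides.

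**3. Size under exact additivity (I = 0).** The documents give neither r nor g, so these are assumptions.

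- g = 1 (flat response over 50–70% of 1RM): shift 0.
- g = 0.786 (effect proportional to mean load): shift −0.214r. At the Statistical analysis section's own benchmarks for Cohen's d, r = 0.2, 0.5 and 0.8 give −0.04, −0.11 and −0.17 SD.
- Other retained shares: g = 0.9 gives −0.05 SD (r = 0.5) or −0.08 SD (r = 0.8); g = 0.5 gives −0.25 or −0.40 SD.

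**4. An illustration tied to the planned effect size.** If r = v and the arm means are 0, r, v and r + v, then f² = (r² + v²)/4. Setting f = 0.40 gives r = 0.566 SD.

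- Interaction shift: −0.214 × 0.566 = −0.12 SD (−0.16 at the 50% load, −0.08 at the 60% load).
- RVT − RT: 0.566 − 0.121 = 0.44 SD instead of 0.57 SD.
- A true synergy of +0.12 SD would appear as no interaction.

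**5. Against sampling error.** In SD units of the 12-week change, the interaction SE is √(4/n).

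- n = 24 per arm: √(4/24) = 0.41; 0.121/0.408 = 0.30 SE.
- n = 19 per arm after 20% dropout (96 × 0.8/4 = 19.2): √(4/19) = 0.46; 0.121/0.459 = 0.26 SE.

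**The case against.** The strongest reply is that this is an open, reasoned design choice. The load difference is stated plainly and justified by tolerance, adherence and safety in older adults. The protocol never says that RVT vs RT isolates vibration, its main aims are framed around the combined programme, and the planned ANOVA has a four-level group factor with no factorial term. Additivity is mentioned only to explain the sample size model. The shift is assumed, modest and possibly zero. If response does rise with load, the bias runs against RVT, so a result favouring RVT would be conservative.

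Much of this stands. The choice is disclosed, no primary test or error rate is affected, and the numbers are illustrations. The f = 0.40 calibration also treats RVT as full dose.

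Three things do not fall away:

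- The sample size calculation already names a group-by-time interaction, so the interaction left for post hoc exploration, introduced straight after the additive hypothesis, is naturally RT-by-VT. Together with the Discussion's aim of amplification, this is a claim about how the modalities combine.
- The rationale explains the lower load but does not remove the confounding. The supporting studies are described as recommending lower starting intensities for vibration training, yet vibration stays at the VT-arm dose and resistance is what is reduced, through week 12.
- The direction is not assured. RVT also differs by progressive loading chosen to help adherence, which could work in its favour, so a positive RVT vs RT difference cannot be credited to vibration alone either.

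Nor can this be left to an analysis plan. The arms and the hypothesis are both fixed in this document, and no analysis can equalize the prescribed doses.

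**Conclusion.** The concern holds. That RVT has the lower prescribed load in 12 of 12 weeks, and that the load term enters both contrasts, follows from the text and simple algebra. The size of the shift does not: it depends on an unknown dose–response and on delivered loads that are only approximate. Under proportional response it is about a fifth of the RT effect, roughly a quarter to a third of a standard error in the calibrated illustration. The problem is what the contrasts estimate, not power, so a larger sample would not cure it. The comparisons with control, and all six pairwise comparisons read as whole programme against whole programme, are unaffected. The wording should be corrected before results are known.

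**What to change.** Keep the arms, tests and sample size, and change only the wording:

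1. In Sample size determination and Statistical analysis, define RVT vs RT as a comparison of two programmes that does not isolate vibration.
2. Name RVT vs VT as the only add-on contrast: it adds the 50–60% resistance programme to identical vibration.
3. State that the exploratory RT-by-VT interaction is not a test of additivity, synergy or antagonism at equal resistance dose.
4. In the Discussion, replace the aim of amplification with the effects of the combined programme, and add the unequal resistance dose to the limitations.

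The cost is a few sentences, plus a narrower claim about the combination.

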#### Educational courses.

Participants in the control group will attend a 60-minute education session twice monthly. Invited experts will deliver these sessions, covering topics such as aging, general health, and sarcopenia—including its definition, etiology, pathophysiology, clinical manifestations, and adverse effects in older adults. These educational courses are intended primarily to maintain participant engagement and minimize dropout. The sessions are standardized, lecture-based, and non-interactive, and do not include individualized exercise prescriptions or dietary counseling. Although it cannot be entirely excluded that exposure to health information may raise awareness or induce minor behavioral changes, previous studies have shown that education-only interventions in older adults generally do not lead to significant improvements in muscle strength, skeletal muscle mass, or physical function [55,56]. Therefore, the risk of overestimating the effects of exercise-based interventions due to this educational component is considered minimal.

